The primary exposure is active enrolment onto the MCTS. Referral alone will not constitute exposure, as not all referred patients commence telehealth monitoring. For enrolled patients, the index date will be defined as the date on which active telehealth monitoring begins. To account for temporal variation in healthcare utilisation and service delivery, telehealth enrolment dates will be grouped into calendar quarters (Q1: January–March; Q2: April–June; Q3: July–September; Q4: October–December). Comparator patients will be selected from quarterly eligibility snapshots comprising individuals who were eligible for MCTS, alive, and registered during the same quarter but who did not enrol onto the service. Calendar quarter will be used as an exact matching variable within the propensity score matching process, ensuring that telehealth participants are compared only with eligible non-enrolled patients observed during the same time period. Additional demographic, clinical, risk, and baseline healthcare utilisation variables will be incorporated into the matching procedure. This approach aims to minimise temporal bias arising from changes in healthcare utilisation, seasonal pressures, COVID-19 recovery effects, admission practices, and service delivery over the study period. The primary analysis will therefore estimate the effect of active enrolment onto MCTS compared with eligible non-enrolment during the same calendar quarter. Findings should be interpreted as representing the effect of the telehealth service model as delivered in routine practice rather than the effect of referral alone or any individual intervention component.

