	30-day readmission	Readmission within 30 days of discharge	SUS-APC
	Mortality	Date of death during follow-up	Primary Care

**Abbreviations:** IMD—The index of multiple deprivation; A&E—Accident & Emergency; CVD—cardiovascular disease; CKD—chronic kidney disease; COPD—Chronic obstructive pulmonary disease; SUS-APC—Secondary uses service admitted patient care; SUS-ECDS—Secondary uses service emergency care dataset; LSOA—Lower layer super output areas

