### Analysis

The study uses two quasi-experimental methods: IPTW-DiD and RD designs. These methods help to reduce the risk of selection bias due to systematic differences between those receiving and not receiving the intervention, in two ways.

The primary approach of the analysis is IPTW-DiD, which is specifically designed to adjust observed differences by reweighting individuals according to their probability of receiving treatment, thereby approximating a pseudo-population in which treatment is independent of observed confounders. The treated cohort will comprise patients who received telehealth, with treatment timing defined by the first quarter in which telehealth was received; patient-quarter observations from this quarter onwards will be considered post-intervention. For untreated patients, comparable index quarters will be assigned to define the pre- and post-intervention periods.

The initial analytic cohort will be restricted to patients aged 50 years or above with at least one relevant long-term condition linked to the telehealth packages: COPD, diabetes, or HF. These eligibility criteria will be applied to both treated and untreated patients to ensure that the control group comprises individuals with a realistic probability of receiving the intervention. To avoid interpreting unobserved quarters as zero healthcare utilisation, the initial analysis will use a balanced panel of patients observed in all 24 quarters across the 6-year study period. The potential selection introduced by excluding patients who die, move away, or register with a GP partway through the study period will be explored in sensitivity analyses.

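### WP1 fixes time zero by date for enrolees but only by quarter for comparators, so a mortality analysis that keeps deaths and counts from the index quarter would be biased, in a direction the text leaves open

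*Protocol article*

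**What the plan says.** All references are to Work package 1 of the protocol article.

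- **Enrolees (Methods).** For enrolled patients, "the index date will be defined as the date on which active telehealth monitoring begins". An enrolee must therefore be alive on a known day inside the quarter.
- **Comparators (Methods).** They come from quarterly eligibility snapshots of "individuals who were eligible for MCTS, alive, and registered during the same quarter but who did not enrol onto the service". The day of the snapshot is not stated.
- **Post-period (Analysis).** Treatment timing is the first quarter with telehealth, and "patient-quarter observations from this quarter onwards will be considered post-intervention". The rule on the comparator side is that "comparable index quarters will be assigned to define the pre- and post-intervention periods". Comparators thus receive a quarter and not a date.
- **Cohort (Analysis).** To avoid reading unobserved quarters as zero use, "the initial analysis will use a balanced panel of patients observed in all 24 quarters across the 6-year study period". The selection this causes, including the loss of patients who die, is left to sensitivity analyses.
- **Outcome (Methods and Table 2).** Mortality is secondary outcome 5, recorded as "Date of death during follow-up". The start and length of follow-up are not given.

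**The concern.** For death, the point at which a patient becomes able to have the event must be the same in both groups. Here it is not. On the quarter clock, the days from quarter start to the start of monitoring are post-intervention time in which an enrolee cannot have died. This is immortal time. A comparator who need only be alive at quarter start is at risk throughout those days. If comparators must instead be alive throughout the quarter, the mismatch reverses: they cannot die in the index quarter, but enrolees can once monitoring has begun.

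Exact matching on calendar quarter does not help, because the mismatch lies inside the quarter. Differencing does not help either: every patient is alive before the index quarter, so there is no pre-period death rate to subtract.

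At stake is outcome 5. Depending on a snapshot day that the text does not fix, a service with no effect on mortality could appear to lower it or to raise it.

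**Working it through.** The plan states no mortality figure, so there is none to reproduce. Its panel length is consistent: 6 years × 4 = 24 quarters.

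**Assumptions (not in the documents).** No true effect; the same constant hazard h in both groups; start dates spread evenly over the 3-month quarter; annual mortality a of 5% to 30%, with h = −ln(1 − a)/12 per month. Deaths are counted from quarter start to month T in both groups.

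**Formulas.**

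- Enrolee alive at start day s, with s uniform on 0 to 3 months: risk = 1 − e^(−hT) × (e^(3h) − 1)/(3h).
- Comparator alive at quarter start: risk = 1 − e^(−hT).
- Comparator alive at quarter end: risk = 1 − e^(−h(T−3)).

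**Example, a = 10%, T = 12.** h = 0.10536/12 = 0.00878. (e^(3h) − 1)/(3h) = 1.0133.

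- Enrolee risk: 1 − 0.9 × 1.0133 = 0.0880.
- Comparator alive at quarter start: 1 − 0.9 = 0.1000. Ratio 0.88.
- Comparator alive at quarter end: 1 − 0.9^0.75 = 0.0760. Ratio 1.16.

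**Enrolee/comparator death ratio under no effect.** The low-hazard column is (K − 0.5)/K or (K − 0.5)/(K − 1), with K the number of quarters.

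| Comparator must be | Months | Low hazard | a = 5% | 10% | 20% | 30% |
|---|---|---|---|---|---|---|
| alive at quarter start | 3 | 0.500 | 0.501 | 0.502 | 0.505 | 0.507 |
| alive at quarter start | 6 | 0.750 | 0.752 | 0.754 | 0.759 | 0.765 |
| alive at quarter start | 12 | 0.875 | 0.878 | 0.880 | 0.886 | 0.893 |
| alive at quarter start | 24 | 0.938 | 0.940 | 0.943 | 0.949 | 0.956 |
| alive at quarter end | 6 | 1.500 | 1.495 | 1.489 | 1.477 | 1.464 |
| alive at quarter end | 12 | 1.167 | 1.163 | 1.159 | 1.150 | 1.141 |
| alive at quarter end | 24 | 1.071 | 1.068 | 1.064 | 1.057 | 1.050 |

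For a snapshot a fraction f of the way through the quarter, the low-hazard ratio is (K − 0.5)/(K − f). It passes through 1 at f = 0.5, so the sign depends on the unstated snapshot day.

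**Simulation, 400,000 per group, a = 10%, comparators alive at quarter start, index quarter among the first 23.**

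| Cohort | Group | Kept | Deaths in index quarter | Deaths within 12 months of quarter start |
|---|---|---|---|---|
| Patients who die kept | Enrolees | 400,000 | 5,226 | 35,272 (8.8%) |
| Patients who die kept | Comparators | 400,000 | 10,519 | 40,099 (10.0%) |
| Balanced panel | Enrolees | 300,141 | 0 | 2,624 (0.87%) |
| Balanced panel | Comparators | 296,128 | 0 | 2,570 (0.87%) |

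With deaths kept, the 12-month ratio is 35,272/40,099 = 0.88. In the balanced panel (taken as alive at the start of quarter 24) the two groups agree, but almost no deaths remain. Even 0.87% is generous, because the 12-month window was allowed to run past quarter 24 for late index quarters.

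**Common time zero.** If each group is followed for equal time from a date on which it is known to be alive, the null ratio is 1.000 under a constant hazard.

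**The case against.** - **The initial analysis is not affected.** This stands. The balanced panel removes deaths before the last quarter from both groups. A reader might infer that the WP1 mortality comparison as planned shows a built-in benefit; for the only cohort the article specifies, it does not. But that panel cannot support outcome 5. A usable mortality analysis must keep patients who die, as the promised sensitivity analyses must, and there the mismatch returns.
- **The quarter clock is written for the patient-quarter model, not for mortality.** This stands in part. Table 2 records a date of death, and it defines age and prior admissions relative to an index date, so some comparator date may be intended. An analysis plan that is not shown may supply it, and following each group from its own dated time zero would give a ratio of 1. But the article gives comparators no dated time zero, and the quarter is the only post-period clock it states.
- **The direction is not determined.** This stands. A snapshot is usually a point in time; near mid-quarter the two errors would roughly cancel. A one-directional claim of apparent benefit is therefore not supported. That the answer turns on an unstated day is itself the reason to fix it.
- **The size depends on assumptions and on follow-up length.** This stands. The ratio is within about 7% of 1 by 24 months on either reading, and the article sets no mortality window. At a given window, though, it hardly moves across 5% to 30% annual mortality.

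**Conclusion.** The concern holds in a conditional form. Time zero is a date for enrolees and a quarter for comparators. In any mortality analysis that keeps patients who die and counts from the start of the index quarter, a null effect would appear as a benefit if comparators need only be alive at quarter start: ratio about 0.75 to 0.77 at 6 months, 0.88 to 0.89 at 12 and 0.94 to 0.96 at 24. It would appear as harm if they must survive the quarter: about 1.14 to 1.17 at 12 months. These figures rest on even enrolment over the quarter and a constant, equal hazard. The balanced panel avoids the bias only by leaving outcome 5 practically unanalysable.

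Three further inferences are tempting but unsupported. The 12-month distortion should not be set against the 15% reduction in the Sample section, which concerns the primary outcome, emergency admissions. Mortality should not be called the main safety outcome, since the article lists it only as the last of four secondary outcomes. Nor does the article say that the WP1 mortality contrast enters the WP4 quality-adjusted life years; WP4 names quality-of-life data, service costs and resource use.

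This should be corrected before analysis: it is a systematic error in a secondary outcome, and the correction is cheap.

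**What to change.** In the WP1 Methods and Analysis sections, assign each comparator an index date within the quarter. Where a matched cohort is used, this can be the matched enrolee's start date; under weighting alone, draw it from the enrolees' start dates in that quarter. Require the comparator to be alive, registered, eligible and not yet enrolled on that date.

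For mortality, start follow-up on that date in both groups, in a cohort not restricted to the balanced panel. An IPTW-weighted time-to-event analysis is one suitable choice.

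The cost is a change of wording in two sections and one programming step; monitoring start dates and dates of death are already planned data items. The downside is a separate person-time dataset for this outcome alongside the patient-quarter panel.

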### Data

The study will use a cohort of monthly data from the Cheshire and Merseyside Secure Data Environment (CM-SDE), the NHS secure data environment that includes linked data across health and care services for all patients registered with a GP in Cheshire and Merseyside. We will use CM-SDE covering a period, 2018–2024 including linked data from the following datasets:

NHS

Primary care dataPrimary care prescribing dataTelehealth services data from the MC telehealth case management system.Secondary care data—Admitted Patient Care (SUS-APC)Community Services Data Set (CSDS)Mental Health Services Data Set (MHSDS)Emergency Care Data Set (ECDS)

Local Authority Adult Social Care

Adult Social Care Dataset (ASCD)

Open data—linked to Lower layer super output areas (LSOAs)

Indices of deprivation

All these datasets are available and can be linked within the CM-SDE. Patient characteristics will reflect individuals at the time of receiving telehealth service and so will correspond to the latest measurement taken during the study period 2018–2024. Table 2 summarises the details of outcome and exposure variables, definition criteria, and datasets from which the variable is derived that would be used in WP1 of the study.

**Table 2 TB2:** Exposure, covariates, and outcome variables for WP1.

Variable category	Variable	Definition/criteria	Data source
Primary exposure	MCTS enrolment	Active enrolment onto the Mersey Care Telehealth Service (Yes/No)	MCTS service dataset
Demographic and baseline characteristics	Age	Age at index date (≥18 years)	SUS-APC
	Sex	Male, Female, Other	SUS-APC
	Ethnicity	White British, Other White, Black, Indian, Pakistani, Bangladeshi, Chinese, Other Asian, Other ethnic group	SUS-APC
	Living alone	Yes/No	Primary Care
	Living with under-18s	Yes/No	Primary Care
	Household size	Number of people in household	Primary Care
	Geography	LSOA 2011	SUS-APC
	Deprivation	IMD 2019	SUS-APC
	Frailty	Fit, mild, moderate, severe frailty	Primary Care
Clinical characteristics	Long-term conditions	Hypertension, cancer, diabetes, CVD, heart failure, CKD, asthma, COPD, depression, schizophrenia, bipolar disorder	Primary Care
Baseline healthcare utilisation	Emergency admissions (previous 12 months)	Count of emergency admissions before index date	SUS-APC
Outcomes	Unplanned emergency hospital admissions	Count of admissions during follow-up	SUS-APC
	A&E attendances	Count of attendances during follow-up	SUS-ECDS
	30-day readmission	Readmission within 30 days of discharge	SUS-APC
	Mortality	Date of death during follow-up	Primary Care

**Abbreviations:** IMD—The index of multiple deprivation; A&E—Accident & Emergency; CVD—cardiovascular disease; CKD—chronic kidney disease; COPD—Chronic obstructive pulmonary disease; SUS-APC—Secondary uses service admitted patient care; SUS-ECDS—Secondary uses service emergency care dataset; LSOA—Lower layer super output areas

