A treatment model will calculate the likelihood of each patient receiving the intervention using baseline socio-demographic variables, comorbidity measures, and 12-month cumulative pre-intervention healthcare utilisation, such as unplanned emergency admissions. For variables that may change over time, baseline or pre-intervention values will be used. Stabilised IPTW weights (Austin and Stuart, 2015) will be used in the DiD model to balance measured baseline covariates and reduce the influence of extreme weights. Covariate balance, weight stability, overlap/common support, effective sample size, and the plausibility of the conditional parallel-trends assumption will be assessed using weighting diagnostics and pre-intervention outcome trends. Comprehensive sensitivity analyses will be performed to evaluate the robustness of all estimates.

To manage the potentially large untreated population, the above eligibility restrictions will be applied before weighting. If the remaining comparison cohort is still too large for the available computing environment, a 5:1 propensity-score matched comparison cohort based on baseline characteristics may be constructed before applying the weighting approach; this will be reported as a computational sensitivity analysis.

Additionally, the RD design (Thistlethwaite and Campbell, 1960) will serve as a secondary complementary analysis, subject to the availability of a documented Johns Hopkins ACG risk score eligibility threshold (NHS England, 2025d) and sufficient observations close to that threshold. Threshold values, temporal changes, and geographical variations will be documented. As RD estimates a local effect among patients close to the eligibility threshold, its findings will be interpreted alongside, rather than as direct confirmation of, the IPTW-DiD estimates.

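### WP1 gives two contradictory rules for when covariates are measured; one of them would admit frailty and diagnoses recorded after enrolment

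*Protocol article*

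**What the plan says.** Four parts of WP1 bear on covariate timing.

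- **Data section, the text introducing Table 2.** "Patient characteristics will reflect individuals at the time of receiving telehealth service", it says, and it draws from this that they "will correspond to the latest measurement taken during the study period 2018–2024".
- **Table 2.** Age is taken at the index date, and prior emergency admissions are a "Count of emergency admissions before index date". Frailty ("Fit, mild, moderate, severe frailty") is listed among the demographic and baseline characteristics but has no measurement date. Long-term conditions, living alone and household size have none either.
- **Analysis section, treatment model.** The probability of treatment is to be modelled "using baseline socio-demographic variables, comorbidity measures, and 12-month cumulative pre-intervention healthcare utilisation". Then: "For variables that may change over time, baseline or pre-intervention values will be used". The weights have the same aim: "Stabilised IPTW weights (Austin and Stuart, 2015) will be used in the DiD model to balance measured baseline covariates".
- **Methods section and the subgroup paragraph.** The index date is the start of active monitoring. The matching variables are listed by type, and only healthcare utilisation is called baseline. Frailty and chronic conditions are proposed as subgroups with no timing rule.

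**The concern.** The Data sentence contradicts itself. A value that describes the patient at enrolment is not, in general, the last value in a multi-year extract. It also contradicts the Analysis section. The two rules produce different datasets, and a programmer working from the Data section and Table 2 would find only the wrong one for the undated variables.

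Frailty and recorded diagnoses can change after enrolment, and an admission may itself lead to new codes. A latest-in-period value may then be partly a consequence of the primary outcome, emergency admissions. Conditioning on it is adjustment for a post-treatment variable. The planned checks need not reveal this: balance would be assessed on the same late values, and pre-intervention trends do not show a distortion that arises after the index date.

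**Working it through.** **1. How far apart the two rules can be.** The Analysis section uses a balanced panel of 24 quarters. If the first four supply the 12-month history, the earliest enrolment is in quarter 5, which leaves 24 − 5 = 19 quarters, or 4.75 years, in which a later value can be recorded. If the history comes from before the panel, enrolment in quarter 1 leaves 23 quarters, or 5.75 years. A balanced panel means every patient is observed through that window. For enrolment near the end of the panel the two rules almost coincide.

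**2. Direction of the bias.** Let *e* be the fitted probability of enrolment and *p* the overall proportion enrolled. The stabilised weights are *p/e* for enrolled patients and *(1 − p)/(1 − e)* for comparators. Suppose enrolment is likelier in frailer patients and an admission after the index date raises recorded frailty. With latest-value frailty, *e* rises for patients who were later admitted. Admitted enrolled patients are then weighted down and admitted comparators weighted up. On the ratio scale,

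DiD = (T_post / T_pre) / (C_post / C_pre),

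so T_post falls and C_post rises without a matching change in the pre-period rates. The estimate drops below 1 with no true effect. Differencing removes gaps that are constant over time, and this one is not.

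**3. Size.** The plan has no figure of its own for this bias. The only yardstick is the target in the Sample section, a relative risk of 0.85 with 80% power. The documents do not give the strength of selection on frailty, the admission rate or its dispersion, or how often an admission changes recorded frailty. All of these are assumed below, and **there is no true effect in any row**.

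| Set-up (assumed) | Frailty used in the weights | DiD rate ratio |
|---|---|---|
| A. Continuous frailty | Baseline | 0.97–1.02 |
| A. Each admission adds 0.1 SD | Latest | 0.90–0.94 |
| A. 0.2 SD | Latest | 0.81–0.88 |
| A. 0.3 SD | Latest | 0.74–0.83 |
| A. 0.5 SD | Latest | 0.65–0.77 |
| B. Four levels as in Table 2 | Baseline | 1.00–1.01 |
| B. Each admission has a 10% chance of moving up one level | Latest | 0.93–0.96 |
| B. 20% chance | Latest | 0.88–0.92 |
| B. 30% chance | Latest | 0.84–0.90 |
| B. 50% chance | Latest | 0.78–0.87 |
| C. Four levels, other data-generating values | Baseline | 0.99–1.01 |
| C. No extra frailty recording under telehealth | Latest | 0.92–1.03 |
| C. Extra recording, hazard +0.1 to +0.3 | Latest | 0.87–0.99 |
| C. Extra recording, hazard +0.8 | Latest | 0.86–0.90 |

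A: 300,000 patients; logit of enrolment −3.2 + 0.9 × baseline frailty; Poisson admissions with gamma heterogeneity (mean 0.3 or 0.6, heterogeneity 0.5 or 1.0); prior admissions in or out of the model. B: prior admissions in the model, no extra recording under telehealth. C: 400,000 patients, prior admissions in the model, single runs.

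Two further results show how much the answer depends on these choices. When the score in A is cut into four categories, an increment of 0.1 SD gives about 0.92–0.98 and 0.2 SD about 0.86–0.92. In C, without extra recording and with the admission effect held fixed, the ratio is 1.01 when enrolment does not depend on frailty and about 0.94 at the strongest selection tried.

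**4. With a true relative risk of 0.85.** Latest-value frailty gave 0.66–0.78 in A and 0.73–0.87 in C. Baseline frailty gave 0.85–0.86 in C.

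**The case against.** The strongest reply is that the section specifying the treatment model already states the right rule. It calls for baseline or pre-intervention values, describes the weights as balancing baseline covariates, and bases the optional 5:1 matched cohort on baseline characteristics. The first half of the Data sentence expresses the same intent. Table 2 ties age and prior admissions to the index date and lists frailty under a baseline heading. On this view the Data sentence is a slip in a condensed article.

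Much of that stands. A reader might infer that post-enrolment frailty and comorbidity do enter the propensity model, and that the planned estimate therefore carries a spurious benefit as large as the target effect. The documents do not support this. Late values enter that model only if the Data sentence is followed against the Analysis section. The size of the bias rests wholly on assumed inputs, and no document figure points to an increment of 0.2 SD or any other value. Nothing links admissions to household size or living alone, so the bias argument is confined to frailty and long-term conditions. Even for those, which come from primary care records, the documents do not say how a hospital admission changes the field.

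The reply does not remove the contradiction. No text gives one section priority. The Data sentence is the only timing statement beside the undated Table 2 variables. The matching variables in the Methods section and the frailty and chronic-condition subgroups have no timing rule of their own, so the sentence about the treatment model does not clearly govern them.

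**Conclusion.** The Data and Analysis sections of WP1 contradict each other on covariate timing, and the Data rule is wrong as written. Followed literally, it would let the primary analysis of the primary outcome condition on values recorded up to several years after the index date, with a likely bias towards benefit. That direction assumes that frailer patients are likelier to enrol and that admissions raise recorded frailty or add diagnoses. The size is undetermined: from negligible to about the 0.85 target, and beyond it under the stronger assumptions (down to 0.65). Baseline values gave about 1.0 in every set-up. The point is a contradiction to settle before data extraction. It is not evidence that the planned analysis is biased by 15%.

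**What to change.** Replace the Data sentence with:

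> Each time-varying characteristic is the most recent value recorded on or before the index date (comparators: the assigned index quarter), within a stated look-back; later values are not used.

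Date frailty, long-term conditions and the household variables in Table 2 accordingly. Apply the same rule to the matching variables in the Methods section and to the subgroup variables. Because the Analysis section counts the index quarter as post-intervention, also state which day of that quarter is the cut-off for comparators. The start of the quarter keeps records that follow an admission in that quarter out of the baseline.

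The cost is a sentence, a few table entries and a date filter in the extract. Slightly more values will be missing, for characteristics first recorded after the index date. No new data are needed, and the change carries out what the Analysis section already intends.
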